### Primary endpoint

The primary endpoint of this study is the improvement in median I-CAT scores at T2 (three months post-initial training), assessing IC acceptance. A 0.5-point increase in the median I-CAT score (from 3.0 to 3.5) represents a shift from the median to the 75th percentile of the previously reported distribution [10,11]. This reduction in IC-related reluctance is considered clinically meaningful, indicating a higher level of acceptance among participants receiving the enhanced educational intervention compared to those undergoing standard clinical practice training. The study is powered to detect this difference at T2, with 80 % power and a 5 % significance level, ensuring that the observed effect is both statistically and clinically significant.

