### Sample size

The sample size for this study was determined to ensure sufficient statistical power to detect a meaningful difference in median I-CAT scores between the intervention and control groups. The primary endpoint aims to demonstrate an improvement in median I-CAT scores from 3.0 to 3.5, which corresponds to an increase from the median acceptance score to the 75th percentile of the previously reported distribution [10,11].

To achieve this, a significance level of 0.05 (5 %) was selected, meaning there is a 5 % probability of a Type I error, where a difference is incorrectly concluded when none exists. A power of 80 % (0.80) was chosen, ensuring that the study has an 80 % probability of detecting a true difference between the groups if one exists, thereby reducing the risk of a Type II error. Based on previous studies and pilot data, a standard deviation of 1 was assumed for the calculation [10,11]. Given these parameters, the sample size calculation was performed using a non-parametric (Mann-Whitney U) test to compare the two independent groups.

The formula used for calculating the required sample size accounts for effect size, significance level, and power. The required sample size per group, denoted as n, is calculated using the equation:(1)$$n=\frac{{\left(Z_{\alpha /2}+Z_{\beta }\right)}^{2}\times \;2\;\times \sigma^{2}}{\Delta^{2}}$$

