In this approach, Z_α/2_ represents the Z-score for the chosen significance level (1.96 for α = 0.05), Z_β_ is the Z-score for the desired power (0.84 for 80 % power), σ² represents variance, and Δ is the effect size, defined as the difference between the 75th percentile and the median of the I-CAT score distribution. The calculations indicate that 64 participants per group are required to achieve the desired statistical power and significance level, resulting in a total sample size of 128 participants. This sample size is based on an effect size of 0.5, calculated as the difference between the two medians divided by the standard deviation. A sensitivity analysis was performed to evaluate how variations in the expected effect size impact the required sample size. For smaller effect sizes ranging from 0.5 to 0.2, the required sample size per group increased, ranging from 64 to 392 participants per group. Given the study objectives and feasibility considerations, the target sample size was determined, assuming an effect size of 0.5, confirming that 64 patients per group are sufficient to ensure reliable and statistically meaningful results.

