
### Statistical plan

The statistical analysis of this study will begin with descriptive statistics to summarize the baseline characteristics of participants, including sociodemographic and clinical data, under intention-to-treat analysis. Continuous variables will be presented using means, medians, standard deviations, and interquartile ranges, depending on their distribution. Categorical variables will be summarized using frequencies and percentages.

Inferential statistical analyses will be conducted to compare outcomes between the enhanced educational intervention group and the standard clinical practice training group. Independent *t*-tests will be used to compare normally distributed continuous variables, while Mann-Whitney U tests will be applied for skewed distributions and for the primary outcome (I-CAT score at T2). Chi-square tests will be used to compare categorical variables between the study groups.

Correlation analyses will be conducted following these comparisons to explore relationships between key study variables. Specifically, associations between IC acceptance scores (I-CAT), adherence levels (I-CAS), urinary symptoms (USQNB-IC), and functional abilities (Autonomy Checklist and motor assessments) will be examined. Depending on the distribution of the data, either Pearson’s correlation coefficient (for normally distributed variables) or Spearman’s rank correlation coefficient (for non-normally distributed variables) will be used. These analyses will help identify how different aspects of the patient experience and clinical characteristics interrelate, providing insight into the factors influencing IC acceptance and adherence.

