To evaluate the robustness of the findings, sensitivity analyses will be conducted, comparing the results of multiple imputations with alternative approaches, such as complete case analysis (where only participants with complete data are analyzed) and single imputation methods [18]. These analyses will ensure that the handling of missing data does not introduce bias into the study conclusions. The extent of missing data, the imputation methods applied, and the results of sensitivity analyses will be transparently reported in all study publications and presentations to ensure scientific integrity and reproducibility.

All statistical analyses will be performed using R (R Core Team, 2023). The significance level (alpha) for hypothesis testing will be set at 5 % (0.05). When multiple comparisons are conducted, appropriate adjustment procedures will be applied to control for Type I error inflation. Two-tailed tests will be employed for all analyses.

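### The primary endpoint is a difference in median I-CAT, but the Mann-Whitney test supports a median claim only under an equal-shape assumption that the protocol does not state

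*Protocol article*

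**What the plan says.** The Sample size section powers the trial to "detect a meaningful difference in median I-CAT scores between the intervention and control groups" and adds: "The primary endpoint aims to demonstrate an improvement in median I-CAT scores from 3.0 to 3.5". It defines the effect size as the difference between the two medians divided by the standard deviation, and "a standard deviation of 1 was assumed for the calculation". The Primary endpoint section repeats the target: "The primary endpoint of this study is the improvement in median I-CAT scores at T2". That section calls a 0.5-point rise in the median clinically meaningful. It also says that powering the study for this difference ensures that the observed effect will be both statistically and clinically significant.

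The decision rule is in the Statistical plan: "Mann-Whitney U tests will be applied for skewed distributions and for the primary outcome (I-CAT score at T2"). The Sample size section names the same test. Tests are at 5%, and "Two-tailed tests will be employed for all analyses". No section states that the two arms are assumed to have the same distribution shape at T2.

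**The concern.** The hypothesis and the decision rule are both fixed on the page, and they address different quantities. The claim is about medians. The Mann-Whitney test addresses θ = P(A>B) + ½P(A=B), with θ = 0.5 under the null. The two coincide only when the arms differ by a pure shift.

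There is reason to doubt a pure shift here. The Primary endpoint section describes the hoped-for effect as less reluctance towards catheterization. If education mainly helps the most reluctant men, the lower part of the distribution moves and the middle and top may not.

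At stake is the wording of the trial's single primary conclusion. The test could be significant with equal medians, or non-significant with a real difference in medians. If the interpretation is chosen only after such a result is seen, it is post hoc.

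**Working it through.** **Inputs from the protocol article.** Medians 3.0 and 3.5, so Δ = 0.5; SD 1 for both arms; two-sided α = 0.05 (Z = 1.96); power 80% (Z = 0.84); 1:1 allocation; 64 per group.

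**Step 1: the plan's own figure.** The printed formula gives n = 2 × (1.96 + 0.84)² × 1² / 0.5² = 15.68 / 0.25 = 62.7, so 63. The two-sample t-test solution is 63.8, so 64. The stated 64 reproduces. The formula uses one SD and one Δ, so it implicitly treats the effect as a shift. For scale, a Mann-Whitney calculation under a normal shift of 0.5 SD gives about 66 to 69 per group (63 / (3/π) = 66; Noether's formula, 69). Simulated Mann-Whitney power at 64 per group is 78 to 79%.

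**Step 2: the quantity tested under the planned effect.** With normal scores, SD 1 and a shift of 0.5, θ = Φ(0.5/√2) = 0.638. This value needs normality as well as a shift. The article states neither, and its figures do not fit a normal score: with median 3.0 and SD 1 the 75th percentile would be 3.0 + 0.674 = 3.67, not 3.5. That does not show unequal shapes.

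**Step 3: equal medians, unequal shapes.** Assume Group B is N(3, 1). In Group A, multiply every distance below 3 by k and leave the upper half alone. Both true medians stay at exactly 3.0. Then θ = ¼ × [2.5 − (2/π) arctan k], and the mean gain is (1 − k) × 0.399. Simulation at 64 per arm, two-sided 5%, 20,000 runs:

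| k | θ | Mean gain | Mann-Whitney rejects |
|---|---|---|---|
| 0.5 | 0.551 | 0.20 | 17% |
| 0.3 | 0.579 | 0.28 | 34% |
| 0 | 0.625 | 0.40 | 68% |

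With equal medians and unequal but symmetric spread (SD 0.5 against 1) the test rejects in about 6%. The discrepancy therefore comes from asymmetric differences in shape.

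**Step 4: the reverse case.** Let Group A be 45% uniform on 0 to 2 and 55% uniform on 3.36 to 5, against N(3, 1). The true medians are 3.5 and 3.0, but θ = 0.49, and the test rejects in only 7 to 8% of trials. This is a constructed extreme. It shows that the implication fails in this direction too.

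**Step 5: coarse scoring.** The article does not give the I-CAT's granularity. If scores are whole numbers and the underlying normal shift is 0.40 to 0.49, both true medians are 3 and the test rejects in 56 to 73% of trials. It is significant with identical sample medians in 26 to 30% of all trials. On a half-point grid with a shift of 0.45 to 0.5 that figure is about 2%.

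**Step 6: the statement about clinical significance.** Under the planned normal shift of 0.5 on a continuous scale, about 37% of the significant trials have an observed median difference below 0.5. Even when the planning model is true, power does not ensure an observed effect of the size called clinically meaningful.

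**The case against.** The strongest reply is that the planning model is itself a shift: one SD, one Δ, and a median that moves from 3.0 to 3.5. Under a pure shift the Mann-Whitney test is a valid test of the median difference. This stands. A reader might infer that the test never tests medians and that a significant result cannot support a median claim; the documents do not support that reading. The shift model is only implicit in a sample size formula, however, and it is not carried into the hypothesis or the conclusion.

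Second, the rejections in Step 3 are not false positives. Group A really does better there, with a mean gain of 0.20 to 0.40, and the whole-number cases contain a real shift. This also stands. The fault is in what a significant result would be said to show. Tied medians would be frequent only with whole-number scoring, and targets of 3.0 and 3.5 suggest, without proving, a finer scale.

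Third, a reader might infer that the test was chosen because the distribution is distrusted. The article gives no reason for using it on the primary outcome, and skewness alone does not break a shift, since two equally skewed arms can differ by one. Nor does any sentence say that a significant test demonstrates a median of 3.5; the article says that the endpoint aims to demonstrate it.

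Fourth, an effect estimate may sit in an analysis plan that is not shown. Its absence is therefore no finding. The mismatch between the printed hypothesis and the printed test remains whatever that plan adds.

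Fifth, θ has no I-CAT units, so relying on it alone would lose the 0.5-point clinical threshold. This is correct, and the fix allows for it.

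**Conclusion.** The point holds in this form: the primary hypothesis and endpoint are a median difference, and the named test supports a median claim only under an equal-shape assumption that the article does not state. Without it, significance shows that Group A scores tend to exceed Group B scores, and no more. The rates of 17%, 34% and 68% with equal true medians are illustrations that rest on assumed shapes, because the documents give no T2 distribution.

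A reader might also infer that the sample size is wrong or that the Type I error is inflated. Neither follows: 64 per group reproduces, and under identical distributions the test is unaffected by this point. The severity is moderate, because it bears on what the trial may conclude and not on whether the test can be run.

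The statement in the Primary endpoint section that powering ensures a statistically and clinically significant observed effect is wrong even under the planning model.

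**What to change.** - In the Sample size, Primary endpoint and Statistical plan sections, state the primary hypothesis as what the test tests, H0: P(A>B) + ½P(A=B) = 0.5 for I-CAT at T2, and base the significance conclusion on it.
- Report the between-arm median difference with a confidence interval, for example by bootstrap, beside the test. The 0.5-point threshold is then judged on the I-CAT scale.
- Claim a median shift from the test alone only if the equal-shape assumption is stated and checked.
- Delete from the Primary endpoint section the statement that powering the study ensures a statistically and clinically significant observed effect.
- If an alternative of about 0.64 is quoted, say that it assumes a normal shift of 0.5 SD.

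The cost is wording and one added interval. The test, the data collected and the 64 per group stay as they are. The change should be made before any comparison of the arms is seen.

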To further investigate factors associated with adherence and secondary outcomes, multivariable analyses will be performed. Logistic regression models will be used to analyze binary outcomes, such as adherence status, while linear regression models will be applied to continuous outcomes, including I-CAT scores. Predictor variables will include sociodemographic factors (e.g., age, education level, socioeconomic status), clinical characteristics (e.g., primary diagnosis, comorbidities), and intervention type (enhanced educational intervention vs. standard clinical training). Interaction terms will be incorporated to assess whether the effects of the intervention differ across subgroups, ensuring a comprehensive evaluation of potential effect modifiers. Model selection will be guided by theoretical considerations and statistical criteria, using stepwise or backward elimination methods to refine the models.

Handling missing data will be an important aspect of the analysis. This study assumes that data are missing at random (MAR), meaning that missingness is related to observed data but not to unobserved data [18]. All instances of missing data will be identified and documented, and patterns of missingness will be analyzed to determine whether they are systematically related to specific variables. Descriptive statistics will be used to summarize the extent and distribution of missing data for each variable.

Multiple imputation will be used as the primary method for handling missing data to minimize bias and preserve statistical power [19]. This approach generates multiple plausible datasets by imputing missing values based on observed data, which are then analyzed separately. The results from these datasets will be combined to produce estimates and confidence intervals that appropriately reflect the uncertainty introduced by missing data. Multiple imputations using chained equations will be performed, suitable for handling various variables, including continuous, binary, and categorical data.

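### Powering the trial for a 0.5-point difference does not ensure that the observed effect is statistically or clinically significant, as the Primary endpoint section claims

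*Protocol article*

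**What the plan says.** The Sample size section of the protocol article sets out "to detect a meaningful difference in median I-CAT scores between the intervention and control groups". The target is "an improvement in median I-CAT scores from 3.0 to 3.5", with an assumed SD of 1. On the error rates, "a significance level of 0.05 (5 %) was selected" and "A power of 80 % (0.80) was chosen". The result is 64 participants per group, 128 in all.

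The Primary endpoint section repeats the 0.5-point shift at T2 and labels it clinically meaningful. It closes by describing the power and significance level as "ensuring that the observed effect is both statistically and clinically significant".

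On analysis, the Statistical plan section says that "Mann-Whitney U tests will be applied for skewed distributions and for the primary outcome (I-CAT score at T2", and that "Two-tailed tests will be employed for all analyses". The same section plans linear regression of I-CAT scores with intervention type among the predictors. For multiple imputation it says: "The results from these datasets will be combined to produce estimates and confidence intervals".

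The Limitations section accepts that the study may lack power if the true effect is smaller than expected.

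**The concern.** The clause gives the design a property it does not have. Power is calculated before the data, on the supposition that the true difference is 0.5. It does not ensure that a trial will reach significance, and it puts no lower limit at 0.5 on the difference seen in a significant trial.

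The practical risk lies in interpretation. If the clause is taken at face value, a significant primary result could be presented as a clinically meaningful gain in acceptance although the estimate lies below the plan's own 0.5-point benchmark. The named primary test gives no check on this by itself, because a Mann-Whitney U test does not return a difference in points to compare with 0.5. Care matters more than usual here because the trial is open-label and its primary outcome is self-reported.

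**Working it through.** **Inputs from the protocol article.** Two-sided alpha 0.05, power 0.80, difference 0.5, SD 1, 64 per group, 1:1 allocation, Mann-Whitney U test on I-CAT at T2.

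**1. Reproducing the sample size.** The article's equation (1) gives n = (1.96 + 0.84)² × 2 × 1² / 0.5² = 7.84 × 2 / 0.25 = 62.7, so 63 per group. The two-sample t-test version gives 63.8, so 64. The stated 64 reproduces. The stated 392 per group for an effect size of 0.2 also reproduces: 7.84 × 2 / 0.04 = 392.

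**2. Smallest significant difference.** The standard error of the difference is 1 × √(2/64) = 0.177.

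- Normal approximation: 1.96 × √(2/64) = 0.346.
- t distribution with 126 df: 0.350.
- As a share of the benchmark: 0.35 / 0.5 = 70%.

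**3. What happens if the true difference is exactly 0.5.** The estimate is centred on 0.5, so it falls below 0.5 half the time.

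| Quantity | Normal critical value | t critical value |
|---|---|---|
| P(significant) | 0.807 | 0.802 |
| P(not significant) | 0.193 | 0.198 |
| P(significant and estimate < 0.5) = P(significant) − 0.5 | 0.307 | 0.302 |
| Share of significant results with estimate < 0.5 | 0.307/0.807 = 38% | 0.302/0.802 = 38% |

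**4. Check with the planned test.** Steps 2 and 3 are on the mean scale, so the Mann-Whitney test was simulated: 20,000 trials of 64 per group, normal data, SD 1, true shift 0.5. The Hodges-Lehmann shift was computed for 5,000 of them.

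- Power was 78%, so 22% missed significance.
- Of the significant results, 37% had a Hodges-Lehmann shift below 0.5, and 37% had a difference in sample medians below 0.5.
- There is no sharp cut-off. The proportion significant was 17% for estimated shifts of 0.32 to 0.34, 47% for 0.34 to 0.36, 67% for 0.36 to 0.38 and 88% for 0.38 to 0.40.

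**5. Sensitivity to the SD.** The threshold is 1.96 × SD × √(2/64). Two other SDs were tried, both assumptions:

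- SD 0.74, which normality would imply for a 0.5-point gap between the median and the 75th percentile: 0.26.
- SD 1.25: 0.43.

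The threshold stays below 0.5 across this range.

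**The case against.** Several points can fairly be made for the plan.

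- **The arithmetic is generic.** In any two-sided 5% trial with 80% power, the smallest significant difference is about 1.96/(1.96 + 0.84) = 70% of the target. This stands: the numbers show no flaw in the design or sample size. They do show that the sentence about the design is untrue.
- **The plan keeps 0.5 as its benchmark.** The Primary endpoint and Protocol validation sections tie clinical meaning to 0.5 points, and the Limitations section admits limited power for smaller effects. A reader might infer that the plan declares any p<0.05 a clinical success, but no section states such a rule. The clause invites that reading, and the other sections do not correct it.
- **An effect estimate may well be planned.** A reader might infer that none is, because the Statistical plan attaches no effect measure to the Mann-Whitney test. The documents do not support that. Regression of I-CAT on intervention type is planned, as are pooled estimates with intervals, and a condensed article may leave the measure reported beside a rank test to an analysis plan not shown here.
- **Imputation.** A reader might likewise infer that multiple imputation cannot be joined to the primary test. The pooling sentence is general and fits the regressions directly. How a rank test is pooled is a detail commonly left to the analysis plan.
- **Medians and the rank test.** The sample size formula uses a common SD and a single difference, which is a location-shift model. Under a pure shift the Mann-Whitney test does address the difference in medians. A significant result with equal medians would need groups of different shape, and nothing in the article shows that here.

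**Conclusion.** The point holds for one sentence. The closing clause of the Primary endpoint section is false on both counts. If the true difference is 0.5, about 20% of trials miss significance (22% in the Mann-Whitney simulation), and about 37-38% of the significant ones show an estimate below 0.5. An observed shift of roughly 0.35 is enough for significance.

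These figures rest on 64 analysed per group, SD 1, a two-sided 5% test and roughly normal data. The 0.35 is approximate and on the mean or location-shift scale.

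The finding does not extend to the sample size, the choice of test, the handling of missing data or the absence of a named effect measure. It is still worth correcting, because it governs what a significant primary result may be said to show.

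**What to change.** Delete the closing clause of the Primary endpoint section, so that the sentence says only that the study has 80% power at the 5% level if the true difference is 0.5.

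Keep the Mann-Whitney test and 64 per group. Beside the test, report the between-group Hodges-Lehmann shift in T2 I-CAT with its 95% confidence interval. State that clinical relevance will be judged by setting that estimate and interval against 0.5, not by p<0.05.

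The cost is a wording change and one extra reported quantity, with no further data. The one real consequence is that a significant result may have to be reported as not shown to be clinically meaningful.
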